## 2. Aims

The primary aim of this study is to assess the efficacy of PFIs in a group of patients with a diagnosis of MDD in terms of: (1) reduction of depressive symptoms; (2) improvement of psychosocial functioning; and (3) increase of social contact. The efficacy of PFIs will also be evaluated in terms of: (1) reduction of relapses and hospitalizations at 18 months post-randomization; (2) improvement of adherence to pharmacological treatments and of patients’ quality of life; (3) reduction of self-stigmatization; (4) improvement of coping strategies and expressed emotion in family members, and reduction of family burden; (5) improvement of quality of life of family members. Finally, we will investigate whether the efficacy of the psychoeducational intervention is mediated by the presence of specific temperamental profiles and childhood traumas.

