### 9.2. Statistical Analyses

The statistical analyses will be conducted in accordance with the intention-to-treat analysis. Missing data will be handled using a last observation carried forward (LOCF) analysis. Descriptive statistics will be calculated for the dependent and confounding variables for both groups. Confidence intervals will be calculated at 95%.

The analytical plan will include the following: (1) the use of generalized estimating equations (GEEs), which will provide an estimation of the impact of the intervention on the primary and secondary outcomes while controlling for multiple confounders (i.e., age, gender, illness duration, number of previous relapses, severity of symptoms at baseline, previous psychiatric admissions, physical and mental comorbidities, presence of psychotic symptoms during acute phases, suicidality, pharmacological treatments); (2) the application of a structural equation model to identify possible mediators and moderators of intervention efficacy (i.e., specific temperamental profiles, the presence of childhood trauma and/or abuse, severity of symptoms at baseline, the patient’s psychosocial functioning at baseline, number of family members, the relatives’ coping strategies and levels of expressed emotions at baseline); and (3) the use of a multivariate logistic regression model to identify predictors of a poor response to the experimental intervention.

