Family Problems Questionnaire—Patients’ and relatives’ versions (FPQ) [55]	Practical and psychological burden	The FPQ is a self-administered questionnaire containing 34 items. These items are rated on a 4-point scale, from 1 (never) to 4 (always).	Patients and relatives	T0, T1, T2, and T3
**Social Network Questionnaire (SNQ) [56]**	**Social contacts**	**The SNQ is a self-administered questionnaire which includes 15 items grouped into 4 subscales (practical support, affective support, social and professional help, and help in an emergency). Items range from 1 (never) to 4 (always).**	**Patients and relatives**	**T0, T1, T2, and T3**
Hamilton Anxiety Rating Scale (HAM-A) [57]	Severity of anxiety symptoms	The HAM-A is a 14-item questionnaire developed to measure the severity of anxiety symptoms, both psychic (mental agitation and psychological distress) and somatic (physical complaints related to anxiety). The score for each item ranges from 0 (not present) to 4 (extreme severity).	Patients	T0, T1, T2, and T3
Morisky Medication Adherence Scale [58]	Adherence to pharmacological treatments	This is a 4-item questionnaire. The response options are yes/no for each item, and a five-point Likert scale is used for the last item.	Patients	T0, T1, T2, and T3
Brief Temperament Evaluation of Memphis, Pisa, Paris, and San Diego (B-TEMPS-M) [59]	Affective temperaments	The B-TEMPS-M includes 35 items and uses a five-point Likert scale.	Patients	T0
Childhood Trauma Questionnaire (CTQ) [60]	Childhood trauma and abuse	The CTQ is a 70-item questionnaire which uses a five-point Likert scale. Ratings are grouped into five subscales: emotional abuse, physical abuse, sexual abuse, physical neglect, and emotional neglect.	Patients	T0
Clinical Global Impression Scale (CGI) [61]	Illness severity (CGI-S), global changes in the severity of symptoms (CGI-C), and therapeutic response.	The CGI-S employs a seven-point scale, from 1 (normal) to 7 (the most severely ill patients). CGI-C scores range from 1 (very much improved) to 7 (very much worse). Treatment response ratings should take into account both the therapeutic efficacy and the treatment-related adverse events, and they range from 0 (marked improvement and no side effects) to 4 (unchanged or worse, and the side effects outweigh the therapeutic effects).	Patients	T0, T1, T2, and T3

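### The GEE covariate list omits each scale's own baseline value, so two of the three primary outcomes and the relatives' scales are estimated less precisely than the collected data allow

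*Protocol article*

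**What the plan says.** Section 2 (Aims) names three primary targets: "1) reduction of depressive symptoms; (2) improvement of psychosocial functioning; and (3) increase of social contact". Table 2 links them to the HAM-D, the PSP and the SNQ (domain "Social contacts"), each collected at T0, T1, T2 and T3. The relatives' scales (FPQ, SNQ, LEE, MANSA, FCQ) follow the same schedule.

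Section 9.2, item (1), sets out one GEE analysis for everything: "estimation of the impact of the intervention on the primary and secondary outcomes while controlling for multiple confounders (i.e., age, gender", then "illness duration, number of previous relapses, severity of symptoms at baseline, previous psychiatric admissions, physical and mental comorbidities", and finally "presence of psychotic symptoms during acute phases, suicidality, pharmacological treatments". The only baseline score in that list that could match a primary outcome is symptom severity, and the scale that defines it is not named.

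Item (2) of the same section does name other baseline scores, but only as possible mediators or moderators in the structural equation model: "the patient’s psychosocial functioning at baseline, number of family members, the relatives’ coping strategies and levels of expressed emotions at baseline".

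Section 3 (Methods) stratifies the randomization by centre, age, sex and educational level. No outcome score is among the factors.

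**The concern.** The T0 score on a scale is usually the strongest single predictor of its later score. A GEE that follows the list uses this information for depressive symptoms, if severity means the HAM-D. It does not use it for functioning, social contact or any relatives' scale. The relatives' outcomes would be adjusted for patient characteristics but not for the relative's own starting point.

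Two things are at stake. Confidence intervals for these outcomes are wider than they need to be. And when the arms differ by chance at T0, which stratification does not prevent for these scores, part of that difference shows up as apparent effect. The three primary outcomes would then not be estimated to the same standard, although the missing values are collected anyway.

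**Working it through.** **Inputs from the protocol.** 384 families, 192 per arm; 15% dropout; estimated requirement 88 per arm; 90% power; two-tailed test (section 9.1). The printed 0.05% is read here as 5%.

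**Inputs assumed.** ρ, the correlation of a scale's T0 value with its follow-up value: 0.3, 0.5, 0.7. r, the correlation of baseline severity with that T0 value: 0 to 0.5, with severity acting only through it. Normal approximation, centre effects ignored.

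**The plan's own figure.** The protocol gives no precision or power figure for the PSP or SNQ. The 176 patients (88 per arm) for the HAM-D cannot be rebuilt, because neither a mean nor an SD is given. The effect it implies can be solved for: d = (1.960 + 1.282) × √(2/88) = 0.489. It would be larger if 176 already contains the clustering adjustment. Evaluable patients: 384 × 0.85 = 326, or 163 per arm.

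**Residual variance.** With severity only it is 1 − (rρ)². With own baseline it is 1 − ρ².

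| ρ | severity only, r = 0.5 | own baseline | cut, r = 0.5 | cut, r = 0 |
|---|---|---|---|---|
| 0.3 | 0.9775 | 0.91 | 6.9% | 9.0% |
| 0.5 | 0.9375 | 0.75 | 20.0% | 25.0% |
| 0.7 | 0.8775 | 0.51 | 41.9% | 49.0% |

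**Power at 163 per arm** = Φ(d√(163/2)/√variance − 1.96), for ρ = 0.5, r = 0.5:

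| d | severity only | own baseline |
|---|---|---|
| 0.20 | 46.2% | 55.0% |
| 0.25 | 64.5% | 74.1% |
| 0.30 | 79.9% | 87.8% |
| 0.35 | 90.4% | 95.4% |
| 0.40 | 96.2% | 98.6% |
| 0.489 | 99.5% | 99.9% |

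The same formula with the other variances at r = 0.5 gives, for d = 0.30, 78.2% to 81.0% at ρ = 0.3 and 82.4% to 96.7% at ρ = 0.7.

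**Chance imbalance.** SE of the baseline difference = √(2/163) = 0.111 SD, so its 95% range is ±1.96 × 0.111 = ±0.22 SD. With no help from severity, an imbalance at that limit moves the effect by ρ × 0.217 = 0.07, 0.11 or 0.15 SD (ρ = 0.3, 0.5, 0.7). With severity in the model the multiplier is ρ(1 − r²), so at ρ = 0.5 and r = 0.5 the shift is 0.375 × 0.217 = 0.08 SD.

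**Simulation of four GEE forms** (300 replicates, 163 per arm, ρ = 0.5, r = 0.4, exchangeable working correlation, 6-month effect):

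| Form | SD of effect | slope on own-baseline imbalance |
|---|---|---|
| T1-T3 as responses, severity only | 0.115 | +0.38 |
| T1-T3 as responses, severity and own T0 | 0.102 | −0.04 |
| T0 also a response, arms free to differ at T0 | 0.120 | −0.54 |
| T0 also a response, arms constrained equal at T0 | 0.104 | −0.06 |

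The simulated variance ratio, (0.102/0.115)² = 0.79, agrees with the formula: 0.75/(1 − 0.04) = 0.78.

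**The case against.** **The list may not be the whole model.** It is headed as confounders. It names neither time nor arm-by-time, and it leaves out centre and educational level although both are stratification factors. A condensed article may leave the rest to a full plan. This stands in part: silence is not an express exclusion. But the covariates are stated rather than deferred, and the same section names baseline functioning and the relatives' baseline scores for a different model. An analyst who follows the list would leave them out of the efficacy model.

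**T0 may enter as a response.** The text does not say. A reader might infer that this would necessarily give a change-score contrast and so would also lose precision. That does not follow. It holds only when the arms may differ at T0. With the arms constrained equal there, the loss all but disappears (0.104 against 0.102).

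**Severity need not mean the HAM-D.** A reader might take it as settled that the HAM-D is protected. The term is undefined, and Table 2 also collects the CGI-S, HAM-A and ISI at T0. The HAM-D is the natural reading, not a documented one.

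**The plan may have ample power.** Section 9.1 says the HAM-D needed the largest sample, so 90% is not the stated power for the PSP or SNQ. A rise from 90% to 95% or more should not be read as the effect on this trial. The small effect cited in the Introduction concerns depressive symptoms. This objection stands. The other listed covariates might also absorb some of the variance that is credited here to own baseline.

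**Randomization protects validity.** It does, on average, and the confidence interval allows for chance imbalance.

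**Conclusion.** The point holds as one of efficiency and not of validity. Followed as written, section 9.2 leaves the PSP, the SNQ and the relatives' scales without adjustment for their own T0 values. The estimates are unbiased on average, but they are less precise than they could be and exposed to chance baseline imbalance.

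How much is lost depends on correlations that the protocol does not give. It is slight at ρ = 0.3, worth about a fifth to a quarter of the residual variance at 0.5, and more than 40% at 0.7. In power, the gain matters only if effects on functioning or social contact are small (d about 0.20 to 0.35), and the protocol states no such effect for either. Near d = 0.49 it is negligible. The document therefore does not show that either outcome is underpowered, and this point does not claim it.

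**What to change.** In section 9.2, item (1), state that each GEE for a scale measured at T0 includes the T0 value of that same scale as a covariate, with T1, T2 and T3 as the responses. For the relatives' FPQ, SNQ, LEE, MANSA and FCQ this is the relative's own score. A near-equivalent alternative is to model T0 as a response with the arms constrained equal at baseline. That form needs a working correlation other than independence, since otherwise T0 contributes nothing to the later estimates.

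Keep baseline symptom severity in the list and name the scale that defines it. If that scale is not the HAM-D, the HAM-D model needs its own T0 value as well.

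Cost: one sentence of analysis wording and one degree of freedom per model. All values are already collected, so no patients, visits or data are added.

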## 10. Discussion

Although most of the relevant studies have been carried out with the families of patients with schizophrenia and bipolar disorder, evidence has shown that family functioning also has a significant impact on the course of MDD [67,68]. Relatives of patients with MDD report high levels of burden, including financial difficulties (which are mainly due to loss of productivity in both patients and caregivers), reduced social contact, problems with marital relationships, emotional exhaustion, and worries about the future. Family members also report high levels of anxiety and depressive symptoms, feelings of loneliness and hopelessness, and insomnia [47]. A direct correlation between family burden and patients’ adherence to treatments has been found, and this further emphasizes the importance of family members as allies in the treatment of patients with MDD.

The coping strategies of relatives are also significantly correlated with patient outcomes and with the mental health and wellbeing of relatives. In fact, the adoption of positive thinking and problem-oriented coping strategies by relatives is associated with a decrease in their levels of anxiety; in contrast, the adoption of avoidant coping strategies increases depressive and anxiety symptoms in caregivers, as well as anxiety in patients [15]. Surprisingly, few reports about family burden in MDD and its consequences for the medium- and long-term outcomes of patients are available. This can be explained by the fact that, in the past, major depression was thought to be a less burdensome mental disorder compared with schizophrenia, bipolar disorder, and substance abuse disorders [69].

It may seem obvious to suggest that interventions aimed at enhancing caregiver well-being and reducing caregiver distress may have a positive impact on patient outcomes [49]. In particular, among family interventions, psychoeducational family interventions are recognized as one of the most effective add-on treatments that can be used in conjunction with pharmacological therapy for people with bipolar disorder and schizophrenia [70,71,72,73], while there is little evidence concerning the efficacy of PFIs in the treatment of MDD. The few available studies report that PFIs contribute to shortened hospital admissions, reduced symptom severity, improved social functioning, and increased subjective well-being [74]. In addition, other studies suggest that psychoeducational family interventions may play a role in the prevention of suicidality and disease recurrence [51,74]. It has to be noted that the most recent meta-analysis of the efficacy of PFIs in patients with MDD [49] included only 301 patients with MDD from five randomized controlled trials. The authors reported that the studies had several limitations, including methodological weaknesses such as a lack of detail concerning the randomization process, a lack of blinding assessments, and low certainty concerning each outcome considered in the studies. Therefore, replications of these RCT results are desperately needed.

Our study will aim to overcome these limitations. In fact, one of the main novelties of the present study is the fact that the efficacy of PFIs will be tested on different clinical outcomes and will not be limited to depressive symptoms, i.e., rather than adhering to a recovery-oriented approach to mental disorders [75], the study will be more in line with the needs and values of patients [76,77,78]. It will also evaluate the efficacy of the experimental intervention on several psychosocial and psychological domains, both in patients and in their relatives. The majority of existing studies have assessed the efficacy of the intervention over the short and middle term, while data concerning its efficacy over a longer term are lacking. For this reason, we included a two-year follow-up assessment in order to verify whether the effects of the intervention, usually seen after 6 and 12 months, are maintained over a longer period. Moreover, a major strength of our trial is its adoption of a well-known and validated family psychoeducational model, which has been adapted for the treatment of patients with MDD. Specifically, the Falloon psychoeducational intervention was initially developed for the community management of schizophrenia [19], and then adapted for patients with bipolar disorder [79]. In these disorders, the efficacy of this model has been well documented in RCTs and in real-world trials. To our knowledge, its efficacy has never been tested in patients with MDD. Major depression may represent an ideal target for this approach since it is highly dependent on stressful life events and on family context [42].

Moreover, to our knowledge, no study has assessed the possible mediators and moderators of the efficacy of PFIs, and this is undoubtedly a novel aspect of the present study. Specifically, in our study, we tested the hypothesis that affective temperaments and childhood traumas can impact the responsiveness of patients to family treatments. It has been reported that affective temperaments play a significant role in influencing the long-term outcomes of affective disorders, and that cyclothymic and irritable affective dispositions are associated with a reduced response to pharmacological and/or psychosocial interventions [80]. Regarding childhood traumas, several studies have reported that the presence of physical and psychological abuse, as well as the presence of traumas during childhood, are associated with worse outcomes in MDD patients, reduced problem-solving and social skills, increased disease burden, and increased risk of suicidality [81]. Patients with childhood traumas may present more severe symptoms, be more reluctant to implement changes proposed during an intervention, and show resistance to pharmacological and psychosocial treatments.

Another novelty of the present study is its multicentric nature. In fact, the 24 centers involved in the study are highly representative of the whole Italian nation. The sample size is very large (a total of 384 families enrolled). To our knowledge, no study so far carried out on the efficacy of PFIs in MDD patients and their relatives has been as representative of an entire European country.

Additionally, in the present trial, assessments will be blinded, meaning that the researchers and statisticians will be unaware of the allocations of the patients and their relatives. We decided to collect a variety of “hard clinical indicators”, including age at onset of mental illness, previous hospitalizations for mental illness, suicide attempts, and alcohol and drug use, all of which will be used as explanative variables. These variables will be used to assess potential moderators of the efficacy of PFIs and will inform us about factors that can potentially mitigate the efficacy of such interventions [82,83].

The clinical breakthrough power of this study consists of several aspects. First, the emphasis is not only on reducing symptom severity, but also on restoring a meaningful life so that patients feel satisfied with their personal and social lives [84]. Subjective feelings of being supported by relatives and friends strongly influence the recovery of patients. In fact, the available data show that 51.2% of patients with major depression consider lack of social support an important complication hindering their recovery [85].

Another innovative aspect of our proposed study is the total duration of the intervention (from 4 to 6 months), which includes an average of 18 planned sessions. In addition, the experimental intervention will be flexible, meaning that the number of sessions and their durations can be modulated according to the specific needs of each family. This is intended to increase the scalability of the intervention under routine conditions.

However, the proposed study has some unavoidable limitations. First, some psychopathological dimensions will be assessed using self-assessment instruments. This is necessary if we want to apply the intervention in real-world settings, where the resources are limited, and long evaluations are very difficult. Second, the total number of delivered sessions will not be standardized. Although this might seem a limitation, according to the original PFI Falloon model, psychoeducation should be adapted to the needs of families and, thus, it cannot be too structured. However, a minimum number of 12 sessions will be delivered in order to overcome this limitation. Moreover, we will not include an assessment of the barriers hindering the implementation of PFIs in the participating centers. This is because the main focus of our study is to explore the efficacy of PFIs for patients with MDD and their family members; the scalability of the intervention can be assessed in a forthcoming study, after its efficacy has been documented. Lastly, another possible limitation is the shorter duration of the intervention provided to the control group. However, most RCTs involving psychosocial interventions explore the efficacy of an experimental intervention against treatment as usual, or against a waiting list (meaning no active comparator), or against no intervention. Thus, we believe that the comparison between two active interventions adds value to our protocol.

## 11. Conclusions

In conclusion, from a clinical perspective, the proposed study has the potential to provide valuable insight into the efficacy and effectiveness of family psychoeducation interventions for patients with MDD and their families. If the intervention proves to be effective in reducing depressive symptoms, improving psychosocial functioning, and reducing relapse rates, it will have to be added to the clinical management of MDD, according to the personalized treatment approach.

## Figures and Tables

**Table 1 brainsci-13-01199-t001:** Timeline of the project.

Month	1	2	3	4	5	6	7	8	9	10	11	12–18	19–36
**Obtaining approval of ethical committees**													
**Training in the use of assessment instrument**													
**Training in the use of interventions**													
**Recruitment of patients and their relatives**													
**Administration of interventions**													
**Follow-up assessments**													

**Table 2 brainsci-13-01199-t002:** Assessments instruments.

Assessment Tool	Assessed Domains	Description	Study Population	Assessment Time-Points
**Patients’ socio-demographic schedule**	**Patients’ socio-demographic and clinical characteristics**	**Recorded information will include illness duration, age at onset, number of affective episodes and previous hospitalizations, age at first hospitalization, number of suicide attempts, age, gender, educational level, occupational status, and pharmacological and psychosocial interventions.** **The information will be compiled by the researcher in collaboration with the patient. If the information is inadequate, or if the researcher is not sure about the patient’s reliability, other sources (e.g., treating physician, relatives) can be consulted.**	**Patients**	**T0, T1, T2, and T3**
**Relatives’ socio-demographic schedule**	**Relatives’ sociodemographic characteristics**	**Recorded information will include age, gender, educational level, occupational status, nature of relationship with the patient, number of years cohabiting with the patient, and mean number of daily hours spent with the patient.**	**Relatives**	**T0**
Hamilton Depression Rating Scale (HAM-D) [53]	Severity of depressive symptoms	The HAM-D includes 17 items. Of these, eight items are scored from 0 (absent) to 4 (severe), while nine are scored from 0 to 2. The total score is the sum of the item scores, and ranges from 0 to 52 points.	Patients	T0, T1, T2, and T3
Personal and Social Performance Scale (PSP) [54]	Psychosocial functioning	The total score (which can range from 0 to 100) can be used to assess the patient’s overall functioning (higher scores indicate higher functioning). Ratings are based mainly on assessments of a patient’s functioning in four main areas: (1) socially useful activities; (2) personal and social relationships; (3) self-care; and (4) disturbing and aggressive behaviors.	Patients	T0, T1, T2, and T3
Family Problems Questionnaire—Patients’ and relatives’ versions (FPQ) [55]	Practical and psychological burden	The FPQ is a self-administered questionnaire containing 34 items. These items are rated on a 4-point scale, from 1 (never) to 4 (always).	Patients and relatives	T0, T1, T2, and T3
**Social Network Questionnaire (SNQ) [56]**	**Social contacts**	**The SNQ is a self-administered questionnaire which includes 15 items grouped into 4 subscales (practical support, affective support, social and professional help, and help in an emergency). Items range from 1 (never) to 4 (always).**	**Patients and relatives**	**T0, T1, T2, and T3**
Hamilton Anxiety Rating Scale (HAM-A) [57]	Severity of anxiety symptoms	The HAM-A is a 14-item questionnaire developed to measure the severity of anxiety symptoms, both psychic (mental agitation and psychological distress) and somatic (physical complaints related to anxiety). The score for each item ranges from 0 (not present) to 4 (extreme severity).	Patients	T0, T1, T2, and T3
Morisky Medication Adherence Scale [58]	Adherence to pharmacological treatments	This is a 4-item questionnaire. The response options are yes/no for each item, and a five-point Likert scale is used for the last item.	Patients	T0, T1, T2, and T3
Brief Temperament Evaluation of Memphis, Pisa, Paris, and San Diego (B-TEMPS-M) [59]	Affective temperaments	The B-TEMPS-M includes 35 items and uses a five-point Likert scale.	Patients	T0
Childhood Trauma Questionnaire (CTQ) [60]	Childhood trauma and abuse	The CTQ is a 70-item questionnaire which uses a five-point Likert scale. Ratings are grouped into five subscales: emotional abuse, physical abuse, sexual abuse, physical neglect, and emotional neglect.	Patients	T0
Clinical Global Impression Scale (CGI) [61]	Illness severity (CGI-S), global changes in the severity of symptoms (CGI-C), and therapeutic response.	The CGI-S employs a seven-point scale, from 1 (normal) to 7 (the most severely ill patients). CGI-C scores range from 1 (very much improved) to 7 (very much worse). Treatment response ratings should take into account both the therapeutic efficacy and the treatment-related adverse events, and they range from 0 (marked improvement and no side effects) to 4 (unchanged or worse, and the side effects outweigh the therapeutic effects).	Patients	T0, T1, T2, and T3
Columbia Suicide Severity Rating Scale (C-SSRS) [62]	Suicidality	The clinician-administered version of the C-SSRS (screening version) will be administered. An individual’s suicidal ideation is rated on a scale from 1 (wish to be dead) to 5 (active suicidal ideation with a specific plan and intent). An individual’s previous suicide attempts are rated on a scale from 1 (actual attempt, defined as “a potentially self-injurious act committed with at least some wish to die, as a result of act”) to 4 (preparatory acts or behavior, defined as “Acts or preparation towards imminently making a suicide attempt”). All patients are rated as positive for suicide attempts if they respond positively to one of the four items assessing suicidal behaviors.	Patients	T0, T1, T2, and T3
Level of Expressed Emotion Scale (LEE) [63]	Expressed emotions	The LEE is a 60-item self-administered assessment instrument. The items are rated as true or false and are grouped into four subscales: (1) intrusiveness; (2) emotional response; (3) attitude toward illness; and (4) tolerance/expectations.	Patients and relatives	T0, T1, T2, and T3
Insomnia Severity Index (ISI) [64]	Insomnia	The ISI is a seven-item questionnaire. Each item is rated on using a five-point Likert scale. It is a brief test that assesses the different components of insomnia.	Patients	T0, T1, T2, and T3
Manchester Short Assessment of Quality of Life for the evaluation of quality of life (MANSA) [65]	Quality of life	The MANSA is a 17-item questionnaire, 12 of which are rated using a 7-point Likert scale, ranging from 1 (“could not be worse”) to 7 (“could not be better”), and 5 of which are rated as either yes or no.	Patients and relatives	T0, T1, T2, and T3
Internalized Stigma of Mental Illness Inventory (ISMI) [66]	Stigma	The ISMI is a 29-items questionnaire for evaluating the subjective experience of stigma.	Patients	T0, T1, T2, and T3
**Family Coping Questionnaire (FCQ) [56]**	**Coping strategies**	**The FCQ is a self-administered questionnaire consisting of 34 items rated using a 4-point scale, from 1 (never) to 4 (always). The items can be grouped into the following 11 subscales: seeking information on a patient’s illness, positive communication toward the patient, relatives’ maintenance of social interests, patient’s involvement in social activities, talking with friends about the patient’s condition, coercion, avoidance, resignation, use of alcohol and drugs, collusion, and searching for spiritual help. A higher score is indicative of a stronger endorsement of each coping strategy.**	**Relatives**	**T0, T1, T2, and T3**

